### **3.2. SECONDARY OBJECTIVES**

Performance evaluation on physical measurement phantoms.

Evaluation of image quality in pulmonary, thyroid, parathyroid and brain scans with DaTSCAN.

### **3.3. MAIN EVALUATION CRITERIA**

The main evaluation criterion will be the image quality evaluation on bone scanning obtained with the new LEHRS GE collimator vs. standard Siemens LEHR collimator (two expert nuclear physicians).

There is no standard criteria for evaluating image quality in scintigraphy. A good quality scintigraphic image (sensitive and good spatial resolution) will present good bone fixation, with low background noise, well defined bone surfaces, and good visualization of interosseous spaces.

We will therefore use a 5-point Likert scale :

- 5 Diagnostic quality - Excellent image quality and resolution (excellent bone fixation, almost non-existent background noise, good visualization of bone surfaces and interosseous spaces)
- 4 Diagnostic quality - Good image quality and resolution (good bone fixation, low background noise, good visualization of bone surfaces and interosseous spaces)
- 3 Diagnostic quality - Acceptable image quality and resolution (good bone fixation, moderate background noise, blurred visualization of bone surfaces and interosseous spaces)
- 2 Suboptimal quality - Limited clinical information (poor bone fixation, moderate to high background noise, poor visualization of bone surfaces and interosseous spaces)
- 1 Non-diagnostic quality (poor bone fixation or almost no bone fixation, high background noise)

For each patient, this score will be established for each image type and for each collimator, e.g. whole body scanning, static imaging, tomoscintigraphy (if performed).

The percentage of examinations judged to be of good quality (scores 4 and 5) will be compared for each collimator and each image type.

### **3.4. SECONDARY EVALUATION CRITERIA**

The secondary evaluation criteria will be:

- Physical measurements of collimator performances on phantoms.
- Evaluation of the signal-to-noise ratio in bone scan images (sacroiliac fixation ratios / soft tissue on whole body scanning) obtained using the two sets of collimators.
- A quantified assessment (Likert scale) of the image quality obtained in lung, thyroid, parathyroid or brain scintigraphic examinations at DaTSCAN.
- An evaluation of the signal-to-noise ratio in brain scan images at DaTSCAN, by comparing the striata/occiput fixation ratios obtained using the two sets of collimators, after automatic analysis and segmentation in DaTQUANT (GE) software.

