| MAIN OBJECTIVE              | Compare image quality obtained with the new LEHRS GE collimator versus a standard Siemens LEHR collimator in bone scan studies.                                                                                                                                                                                                                                                                                                                                                              |
| SECONDARY OBJECTIVES        | Evaluation of image quality in pulmonary, thyroid, parathyroid and brain scans with DaTSCAN.

Performances evaluation on physical measurement phantoms.                                                                                                                                                                                                                                                                                                                                |
| MAIN JUDGMENT CRITERION     | Rate of images obtaining a score greater than or equal to 4 on visual image quality analysis (on a 5-point LIKERT scale).                                                                                                                                                                                                                                                                                                                                                                    |
| SECONDARY JUDGMENT CRITERIA | Signal-to-noise ratio measurements on patient acquisitions.

Physical performances of the new LEHRS collimator using physical measurement phantoms.                                                                                                                                                                                                                                                                                                                                    |

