## 2. CONTEXT AND SCIENTIFIC JUSTIFICATIONS

---

Scintigraphic examinations allow to map, in vivo, the biodistribution of a radiopharmaceutical drug, an analogue of a molecule of interest.

Image of the distribution, in the body, of the radiopharmaceutical drug is obtained by detecting the gamma rays emitted by the radioelement used for its marking.

The addition of a collimator (perforated grid) in front of the detectors is needed to select the most informative gamma photons whose direction is orthogonal to the detector.

The choice of the collimator used is based on a compromise between two parameters:

- The thickness and depth of septa. Higher is the energy of the emitted gamma photon (specific to each radioelement), higher is the probability that this photon will pass through material, especially the walls (septa) of the collimator. This septal penetration reduces the spatial resolution and image quality. For this reason, collimators are classified into three main categories, according to the increasing thickness of their septa : low energy (LE), mean energy (ME) and high energy ("high energy" HE)
- The width and number of holes. Large holes increase the sensitivity of the gamma camera but reduce the number or thickness of septa for a constant detector surface. A good sensitivity allows to reduce the examination time but with an alteration of the resolution.

The majority of nuclear medicine examinations use radiopharmaceutical drugs (labelled with technetium 99m, emitting gamma photons, 140keV energy peak) and require the use of low energy collimators (LE). There are large versions of this kind of collimators, the first one promotes sensitivity and the second one promotes resolution (LEHR for "Low Energy High Resolution").

We want to evaluate a new intermediate kind of collimators (LEHRS for "Low Energy High Resolution and Sensitivity", GE) which is design to enhance sensitivity without compromising resolution. The expected degradation of the resolution is compensated by computer correction algorithms.

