#### **4.4. BENEFIT / RISK**

Participation to this study does not create any additional risk for the patient, since the completion of the 2nd scintigraphy does not change the posology, mode and frequency (single injection) of the injected radiopharmaceutical drug.

The patient will maybe benefit from image quality improvement and an exam review by 2 expert physicians. The only constraint for the patient will be an extended examination time of 15 to 30 minutes, compared to a "standard" examination, without any further invasive procedures or additional irradiation.

Collectively, image quality improvement with this collimator could reduce the duration of exams and/or the posology of radiopharmaceutical drugs (improvement of patient dosimetry).

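### The two patient-level criteria called 'signal-to-noise ratio' are target-to-background contrast ratios with no noise term, so they cannot support a conclusion about signal-to-noise

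*Protocol*

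**What the plan says.** Section 3.4 of the Protocol lists two secondary criteria under the name signal-to-noise ratio. The bone criterion is "Evaluation of the signal-to-noise ratio in bone scan images (sacroiliac fixation ratios / soft tissue on whole body scanning". The brain criterion is "An evaluation of the signal-to-noise ratio in brain scan images at DaTSCAN, by comparing the striata/occiput fixation ratios", with segmentation done automatically in DaTQUANT. The Executive Summary gives only the label, "Signal-to-noise ratio measurements on patient acquisitions", and no definition. No standard deviation, variance, coefficient of variation or other measure of noise is attached to these criteria, or appears anywhere else in the Protocol.

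Section 2 says what the new collimator is for: it is a device "which is design to enhance sensitivity without compromising resolution". It adds that "The expected degradation of the resolution is compensated by computer correction algorithms". Section 4.4 states the hoped-for collective benefit: "image quality improvement with this collimator could reduce the duration of exams and/or the posology of radiopharmaceutical drugs".

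Section 3.3 treats uptake and noise as separate attributes of an image. The wording for a Likert score of 4, for example, is "good bone fixation, low background noise, good visualization of bone surfaces and interosseous spaces".

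**The concern.** The name and the definition describe different properties. Sacroiliac over soft tissue, and striata over occiput, say how strongly the target stands out from its surroundings. They do not say how noisy the image is. A collimator that collects more counts raises the numerator and the denominator together, so the ratio does not respond to the property the device was built to improve.

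The misreading can go either way. Equal ratios would be reported as equal signal-to-noise even if noise differed between the two systems. A change in contrast, from loss of resolution or from the correction algorithms, would be reported as a change in signal-to-noise. The same holds for examination time and injected activity: a quantity whose expected value does not move when counts are halved cannot inform the hope expressed in section 4.4.

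**Working it through.** The Protocol states no figure for these criteria, so there is none to reproduce. The check is algebra, followed by an illustration.

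**Inputs from the Protocol**
- The two ratio definitions (section 3.4).
- The design aim of higher sensitivity with resolution maintained (section 2).

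**Assumptions, because the Protocol gives no values**
- 'Fixation ratio' is read as mean over mean; the region statistic is not stated.
- Sensitivity gain g of LEHRS over LEHR between 1.2 and 2.0, acting equally on both regions.
- Poisson counts.
- The count levels and true ratios shown below.

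**Step 1. Invariance of the ratio.** Let mean counts be B in the target and S in the background. With gain g they become gB and gS, and the ratio is gB/gS = B/S. This holds for any g, whether it comes from sensitivity, acquisition time or injected activity.

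**Step 2. A measure with a noise term.** Under Poisson counts, (gB − gS)/√(gS) = √g × (B − S)/√S, so it grows as √g. With B = 100 and S = 20:

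| g | Ratio | (B − S)/√S | Change |
|---|---|---|---|
| 0.5 | 50/10 = 5.0 | 40/√10 = 12.6 | −29% |
| 1.0 | 100/20 = 5.0 | 80/√20 = 17.9 | reference |
| 1.3 | 130/26 = 5.0 | 104/√26 = 20.4 | +14% |
| 2.0 | 200/40 = 5.0 | 160/√40 = 25.3 | +41% |

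**Step 3. Simulation.** 20,000 replicates, regions of 100 pixels, noise measured as the pixel SD in the background region.

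| True ratio, background counts per pixel | Measure | g = 1.0 | 1.2 | 1.5 | 2.0 |
|---|---|---|---|---|---|
| 4, 20 | Ratio | 4.002 | 4.002 | 4.002 | 4.001 |
| 4, 20 | (mean target − mean background)/SD | 13.53 | 14.80 | 16.56 | 19.12 |
| 2, 5 | Ratio | 2.005 | 2.003 | 2.001 | 2.002 |
| 2, 5 | (mean target − mean background)/SD | 2.26 | 2.47 | 2.76 | 3.19 |

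The noise-based measure rises by about 9%, 22% and 41%, as √g predicts. What falls for the ratio is only its scatter between replicates (SD 0.100 to 0.071 in the first setting), and a paired comparison of ratios does not test that.

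**Step 4. What does move the ratio.** If a fraction c of the excess over background is recovered, the ratio becomes 1 + (R − 1)c. With R = 4, c = 0.9 gives 3.7 and c = 0.8 gives 3.4. The ratio therefore responds to contrast.

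**Step 5. Sensitivity to the reading.** If the target maximum were used in place of the mean, the ratio would depend on noise, but in the wrong direction. In the first setting, maximum over mean falls from 5.17 at g = 1 to 4.82 at g = 2, although the image is less noisy.

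**The case against.** The strongest reply is that the ratio is a sensible quantity for this study and only its name is loose. The design is non-inferiority, section 2 expects some loss of resolution, and a loss of contrast is what such a ratio can detect. Section 3.4 also prints the regions beside the label, so a reader can see what is computed. This stands as far as it goes: the ratio should be kept. It does not rescue the name, because the summary carries the label alone and section 3.3 itself separates uptake from background noise.

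A second reply is that the suggested alternative has faults of its own. Pixel SD depends on pixel size and processing, the two cameras come from different vendors, and correction algorithms are part of the new system. Noise may then not be Poisson, and the gains shown above need not apply exactly. That is correct, and it limits how the added measure may be interpreted.

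A reader might also infer three stronger points that the Protocol does not support:
- **That the trial cannot see noise at all.** Every level of the Likert scale in section 3.3 rates background noise, and section 3.4 lists phantom measurements of collimator performance as a criterion in their own right.
- **That this is the only quantitative patient-level endpoint.** There are two such ratios, and Likert scores are recorded for each patient.
- **That the ratio mainly tracks which scan came second, through soft-tissue clearance.** The Protocol gives no clearance rate. Section 5.5.1 lets the first camera follow the appointment slot and closes a camera to inclusion at 50% of the study population, which would roughly balance order overall. That balance is not stated for each examination type, but scan order is a separate matter from the missing noise term.

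**Conclusion.** The concern holds for both criteria. They are contrast ratios under a signal-to-noise label. That their expected value does not change with counts follows from the definition and needs no assumption about the size of the gain; it needs only the mean-over-mean reading and a gain common to both regions. The increases of 14% and 41% are illustrations under assumed Poisson counts and gains, and are not estimates for this collimator.

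The consequence is confined to what may be concluded from two secondary criteria; the primary comparison is untouched. It matters more for the bone criterion, since 70 of the 85 planned patients have bone scans. The remaining 85 − 70 = 15 are shared among four other examination types, so the DaTSCAN ratio can be little more than descriptive.

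**What to change.** 1. In section 3.4, rename both criteria 'target-to-background contrast ratio', change the label in the Executive Summary to match, and state the region statistic (mean over mean, if that is what is meant).
2. For bone scans, add a noise-based measure from the same regions, (mean sacroiliac − mean soft tissue)/SD of soft-tissue pixels, compared within patient between the two systems.
3. For DaTSCAN, add the corresponding measure only if pixel data can be exported from the software. Otherwise rename only.
4. State beside the added measure that pixel SD also depends on pixel size and on each vendor's processing, so it describes the camera, collimator and software together and not the collimator alone.

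The cost is two wording changes and one further statistic per bone scan from regions already drawn. No extra acquisition, injection or patient is needed. If only the renaming is done, the reporting error is removed, but the study then has no region-based measurement of noise in patients.

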## **4. STUDY POPULATION**

---

### **4.1. INCLUSION CRITERIA**

Any patient referred for bone, lung, thyroid, parathyroid or brain scans with DaTSCAN.

#### **4.2. CRITERIA FOR NON-INCLUSION**

- Minors,
- Pregnant women or women at risk of pregnancy (beta-HCG dosage will be performed 48 hours before examination for patients in the second part of the cycle or in the absence of contraception),
- Patients with known renal insufficiency,
- Patients with pain, EVA >4,
- Patients who cannot benefit from a standard good quality scintigraphic examination (agitated patients...)
- Person under guardianship or curatorship

#### **4.3. RECRUITMENT PROCEDURES**

Study will be proposed to all eligible patients, referred for bone, lung, thyroid, parathyroid or brain scans with DaTSCAN. Each patient will receive the study information leaflet.

The patient will be seen by a nuclear medical physician of the team as soon as he arrives in the nuclear medicine department, before exam. The study protocol and the various informations will then be explained to him.

Informational documents will be left for the patient to continue to review, in greater detail, during the waiting time before acquisitions are completed (approximately 2 hours after the injection of the radiopharmaceutical drug).

If at the end of this additional reflection period, the patient still agrees to participate to the study, his consent form will be collected by the manipulator, who will put it in the study folder. In case of non agreement, only standard examination will be performed and the patient will not participate to the study.

#### **4.4. BENEFIT / RISK**

Participation to this study does not create any additional risk for the patient, since the completion of the 2nd scintigraphy does not change the posology, mode and frequency (single injection) of the injected radiopharmaceutical drug.

The patient will maybe benefit from image quality improvement and an exam review by 2 expert physicians. The only constraint for the patient will be an extended examination time of 15 to 30 minutes, compared to a "standard" examination, without any further invasive procedures or additional irradiation.

Collectively, image quality improvement with this collimator could reduce the duration of exams and/or the posology of radiopharmaceutical drugs (improvement of patient dosimetry).

## 5. RESEARCH DESIGN

---

### 5.1. RESEARCH METHODOLOGY

Monocentric, comparative, non-inferiority study, with intra-patient comparisons (acquisition vs LEHR Siemens reference collimator, for each patient).

Interpretation of image quality in double-blind mode.

### 5.2. SPECIFIC PROCEDURES FOR RESEARCH

The management of patients included in this study is based on the standard conventional management.

It will simply be carried out, with the radiopharmaceutical drug already injected for the standard examination, a larger number of acquisitions (taken with the set of two collimators to be evaluated), but without additional irradiation.

In the case of CT scan performed for the standard examination (depending on the clinical indication of the examination), only one CT scan will be performed for the two acquisitions.

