## **2.2. DESCRIPTION OF THE STRATEGY STUDIED**

Exam protocol will be conforme to French and international medical societies recommandations. According to indication, early images will be realized after radiopharmaceutical drug injection. Late bone scan images will systematically be realized 2 hours after injection (for the radiopharmaceutical drug used in our department), mentioned as whole-body scan. This acquisition is often complemented by additional planar acquisitions, focused on a region of interest (most often the painful area and/or pathologic bone uptake).

In some cases, a tomoscintigraphy will be performed, allowing to obtain 3D volume scintigraphy images, improving the sensitivity of detection of small abnormal bone fixations. This acquisition of tomoscintigraphy will be associated with CT scans for more accurate anatomical localization.

In addition to this standard examination, the patient's participation in the research protocol will involve the creation of complementary images with the new collimator : a second whole body

[figure not shown]

scan, a static acquisition, and in cases where it has been requested for the standard examination, a tomoscintigraphy (without CT in this case, to maintain dosimetry equivalent to the standard examination).

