### 5.5.1. Drawing of lots

A draw will not be carried out because the standard examination will always be carried out first in order not to cause a loss of chance if the examination is stopped (patient with pain...). This also allows the patient to refuse to participate in the study at the end of his or her standard examination. The protocol will be adapted to compensate for the delay between the two examinations (increased acquisition time in proportion to the radioactive decrease).

Patients will be included consecutively. Images will be realized first on the GE camera, equipped with the LEHRS collimator, or on the Siemens camera, with LEHR collimator, depending on his initial appointment slot. However, when 50% of the study population has been achieved on one of the two cameras, the inclusions will only continue on the other.

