### 5.5.2. Blinding method

[figure not shown]

The imaging data will be anonymized, by a person who will not be part of the image reviewers, to remove all information related to the patient's identity from the DICOM fields of the image (metadata). A number will be assigned to each patient, using a randomization table. The patient's identity - anonymization number correspondence will be collected in a specific database.

Images will be read at the end of the inclusions, from the anonymized data, by two senior doctors, on a post-processing console. The anonymization method will not identify the patient's identity or the type of device used (LEHR or LEHRS collimator).

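### The two tomoscintigraphies of a pair can differ in CT as well as in collimator, and the blinding procedure in section 5.5.2 does not make them alike

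*Protocol*

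**What the plan says.** All references are to the Protocol.

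- **CT.** Section 2.2 pairs the standard tomoscintigraphy with a CT, to help place findings anatomically. The research examination adds "a tomoscintigraphy (without CT in this case, to maintain dosimetry equivalent to the standard examination". Section 5.2 makes the CT depend on the clinical indication and adds that "only one CT scan will be performed for the two acquisitions".
- **Scoring.** Section 3.3 has the 5-point score given for each collimator and each image type, with the types listed as "whole body scanning, static imaging, tomoscintigraphy (if performed". The share of scores 4 and 5 is then compared by collimator within each image type.
- **Blinding.** Section 5.1 calls the reading double-blind. Section 5.5.2 states: "The anonymization method will not identify the patient's identity or the type of device used (LEHR or LEHRS collimator". The procedure it describes is the removal of patient-identity information from the DICOM fields. It does not mention CT or fused images.
- **Which device has the CT-free scan.** Section 2.2 says that "the patient's participation in the research protocol will involve the creation of complementary images with the new collimator". Section 5.5.1 says that "the standard examination will always be carried out first", but also: "Images will be realized first on the GE camera, equipped with the LEHRS collimator, or on the Siemens camera, with LEHR collimator", according to the appointment slot. It adds a balancing rule: "when 50% of the study population has been achieved on one of the two cameras, the inclusions will only continue on the other".

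**The concern.** Within a tomoscintigraphy pair, the collimator is meant to be the feature under comparison. As written, the pair can also differ in CT: the standard scan has one and the research scan does not. If readers open the data sets as acquired, two things could follow.

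First, the presence of a CT shows which scan was the standard one. Removing identity metadata does not hide that. If the standard scan is always on the same camera, it also shows which device was used.

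Second, anatomical support from CT could affect the score itself. The scale in section 3.3 asks how well bone surfaces and the spaces between bones are seen, and a fused CT might plausibly influence that judgement. A difference in the good-quality rate would then combine a collimator effect with a CT effect.

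At stake is the tomoscintigraphy comparison, one of the image-type comparisons under the main criterion of a non-inferiority study.

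**Working it through.** The protocol gives no figure to reproduce here: no number of tomoscintigraphies, no expected rate and no margin. The check therefore sets out what each reading of the text implies.

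**Inputs**
- q: share of CT-bearing tomoscintigraphy pairs in which the CT belongs to the LEHR scan. Section 2.2 implies q = 1. Section 5.5.1 implies q of about 0.5 overall.
- d: effect of having a CT on the probability of a score of 4 or 5. Not in the protocol; taken as 5, 10 or 15 points.
- m: number of pairs whose standard scan had a CT. Not in the protocol; taken as 10, 20, 35 or 50 out of the 70 bone-scan patients (Executive Summary).
- First camera: assumed to split 35/35 among those 70 under the 50% cap.

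**Formulas**

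A CT effect raises the LEHR rate by q·d and the LEHRS rate by (1 − q)·d. The difference LEHRS minus LEHR therefore shifts by (1 − q)·d − q·d = (1 − 2q)·d. If only a share c of the tomoscintigraphy pairs has a CT, the shift is multiplied by c. A reader who uses CT presence to guess the device is right with probability max(q, 1 − q).

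**Results**

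| Reading | q | Device guess correct | Shift for d = 5 / 10 / 15 points |
|---|---|---|---|
| Section 2.2 | 1 | 100% | −5 / −10 / −15 |
| Intermediate | 0.75 | 75% | −2.5 / −5 / −7.5 |
| Intermediate | 0.6 | 60% | −1 / −2 / −3 |
| Section 5.5.1 | 0.5 | 50% (no information) | 0 / 0 / 0 |

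**Chance imbalance under section 5.5.1**

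The cap applies to the whole study population and not within tomoscintigraphy patients. If m of the 70 patients fall at random with respect to first camera, the hypergeometric distribution gives:

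| m (assumed) | 95% range of q | Largest shift in that range, as a multiple of d | For d = 10 points |
|---|---|---|---|
| 10 | 0.20 to 0.80 | ± 0.60 | ± 6 |
| 20 | 0.30 to 0.70 | ± 0.40 | ± 4 |
| 35 | 0.37 to 0.63 | ± 0.26 | ± 2.6 |
| 50 | 0.42 to 0.58 | ± 0.16 | ± 1.6 |

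The multiple is 2q − 1 at the upper limit, for example 2 × 0.70 − 1 = 0.40. First camera follows the appointment slot and not a draw, so the random-fall assumption may be optimistic.

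**The two sections side by side**

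Section 2.2 attaches the added, CT-free images to the new collimator. Section 5.5.1 lets the first examination, which is the standard one, take place on the LEHRS camera. In those patients the added images would be the LEHR ones. Both cannot hold for every patient, and which one applies decides between the first and last rows of the first table.

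**The case against.** The strongest reply is that the protocol is silent here, and silence is not a fault.

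- No section says that readers are shown CT or fused images, or that CT data are used in reconstruction. The only stated use of the CT is anatomical localization, and the scale describes scintigraphic features only.
- Section 5.5.2 commits to the device not being identifiable, and nothing in the plan sets out to break that.
- The examination schemes in section 5.5 and a figure in section 5.5.2 are not shown in the text available, so their content is unknown.
- Section 5.2 can be read as one CT serving both acquisitions.
- Reading details are often left to a reading manual or an analysis plan.

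Much of this stands. A reader might infer that blinding fails and that the comparison is biased against LEHRS. The documents do not support that. It would require both that readers see the CT, which is nowhere stated, and that section 2.2 prevails over section 5.5.1. Under section 5.5.1, CT presence marks the order of the scans and not the device.

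What remains is that section 5.5.2 asserts a result without describing a step that delivers it for CT. Section 2.2's exclusion of CT from the research scan fits poorly with the shared-CT reading. Even if one CT did serve both, the protocol states no common rule for its use. Section 5.5 is also where this protocol sets out its measures against bias, so the rule belongs there.

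**Conclusion.** The point holds as an unsecured safeguard. The CT asymmetry within a pair is written into the plan, both scans are scored under the main criterion, and the described masking does not remove the asymmetry.

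The size is conditional. If section 2.2 governs and readers see the CT, the device is identifiable in every affected pair, and the full CT effect d counts against LEHRS. If section 5.5.1 governs, the expected bias is about zero, with a possible residual of roughly 0.4·d in either direction for an assumed 20 affected patients. If readers do not see the CT and it plays no part in reconstruction, there is no effect. The values of d and m are assumptions throughout, so no point estimate of bias should be quoted.

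The scope is limited to tomoscintigraphies whose standard scan had a CT. Section 3.3 compares each image type separately, so the whole-body and static comparisons are untouched.

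**What to change.** 1. Add a rule to section 5.5.2, for example: *Tomoscintigraphies from both collimators are scored on emission-only images, with no CT or fused display. Both are reconstructed with the same use of CT data (most simply none) and shown under identical display settings. The CT remains available for clinical reporting.*
2. Reconcile section 2.2 with section 5.5.1 on which device carries the CT-free acquisition, and use the same description in both places.

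The cost is one extra emission-only reconstruction or export per tomoscintigraphy, plus the added text. No further CT, irradiation or patients are needed. Section 5.5.2 places the reading after the end of inclusions, so the rule can be fixed before any image is scored. The downside is that the scored image will differ from the fused image used in clinical practice.
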